## Analyses

We will provide a descriptive analysis of three groups: callers who chose to bypass the waiting line, callers who chose not to bypass the line and callers from the control group. In addition, we will perform univariate analyses comparing the callers in the three groups (e.g. caller characteristics, reason for encounter and motives for calling). Descriptive analyses will be performed using Student’s *t*-test for data following a normal distribution, Mann–Whitney *U*-test for non-normally distributed data and chi-square test for categorical data. For our primary outcome measures, i.e. patient satisfaction and feeling of safety, we will perform intention-to-treat analyses and subgroup analyses. Associations between relevant use of the emergency access button, level of urgency (as assessed by triage professional) and caller characteristics will be explored by multivariate binomial regression taking clustering at triage professional level into account. Associations between callers choosing to bypass the line, satisfaction with having the option and the reasons for using the option will be assessed using multivariate binomial regression models.

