## Study period and power calculations

We performed power calculations to assess the number of respondents needed to answer our main research question on feeling of safety and to assess the expected duration of the study period to ensure valid estimates of emergency button use. As both the number of button users and the response rate of caller questionnaires can influence the length of the study period, we performed two power calculations: one based on response rate and another based on number of button users.

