### Response rate

Our main outcome measures on satisfaction and feeling of safety will both be measured by a 5-point Likert scale. We want to be able to detect a mean difference of at least 0.3 between button users and non-users. If we assume that the sample standard deviation is 1, the significance level is 5%, the power is 95% and given a mean of 3, we need a total of 290 completed patient questionnaires for each of the three groups to be able to detect a difference of 0.3 between two groups.

Our field test showed that approximately 40% of all callers chose not to participate in the study, and 10% did not type in their CRN, thus leaving them out of the randomization (Fig. 2). In 2014, approximately 700,000 contacts were made to the OOH-PC in the Central Denmark Region [18]. This gives us a study population of 50% out of 700,000, i.e. 350,000 for one year. Of these, 50% would be randomized into the intervention arm (175,000); 3% of these would use the emergency button (5,250). The field test also showed that approximately 70% of the triage personnel chose to participate in the study (3,675) and that the response rate of the caller questionnaire was approximately 40% (1,470). Thus, we will get 123 answered questionnaires from button users per month if the above-mentioned conditions are taken into account. To collect 290 questionnaires per group, the duration of the study period must be approximately 2.4 months.

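### The protocol does not settle which outcome or which contrast decides the trial, while 290 per group allows for only one two-sided 5% test of one outcome

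*Protocol article*

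**What the plan says.** **Lead outcome.** Under Study period and power calculations, the protocol article sizes the trial "to answer our main research question on feeling of safety", which is one outcome. The Response rate subsection then has two: "Our main outcome measures on satisfaction and feeling of safety will both be measured by a 5-point Likert scale". The Analyses section also has two: "For our primary outcome measures, i.e. patient satisfaction and feeling of safety, we will perform intention-to-treat analyses and subgroup analyses". The Primary outcome measures list puts satisfaction and feeling of safety together in one entry, next to bypass frequency and relevance.

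**Contrast.** The Primary outcome measures entry compares button users with non-users. The Response rate subsection agrees: "We want to be able to detect a mean difference of at least 0.3 between button users and non-users". The Analyses section plans intention-to-treat and subgroup analyses of the same outcomes, and describes three groups: "callers who chose to bypass the waiting line, callers who chose not to bypass the line and callers from the control group".

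**Test level and size.** The only significance level is in the sample-size assumptions: "the significance level is 5%, the power is 95% and given a mean of 3", with "If we assume that the sample standard deviation is 1". The resulting target, for a comparison of one pair of groups, reads "we need a total of 290 completed patient questionnaires for each of the three groups to be able to detect a difference of 0.3 between".

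**The concern.** Users and non-users both belong to the intervention arm. Comparing them is therefore not the intention-to-treat comparison, which sets that whole arm against control. Two different contrasts are attached to the same two primary outcomes, and the article does not say which result decides if they disagree. They could disagree easily: with about 3% of the arm expected to press the button, users might be clearly more satisfied than non-users while the arms hardly differ.

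The outcomes also have no order. Feeling of safety is called the main question in one place and is one of two equals in three others. A reader following the article could take any of four results (two outcomes on two contrasts) as the primary result, before any subgroup analysis. The trial is described as a superiority trial, and the one level it states would not hold across that set.

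**Working it through.** **1. The plan's own figure.** Inputs from the Response rate subsection: difference 0.3, standard deviation 1, significance level 5%, power 95%. Taking the level as two-sided:

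n per group = 2 × (1.960 + 1.645)² / 0.3² = 288.8, or 289, against the stated 290.

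A one-sided 5% test would need 241. A two-sided 2.5% test (5% split over two outcomes) would need 336. So 290 spends the full two-sided 5% on one comparison of one outcome.

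**2. Two outcomes on one contrast.** Assume each is tested two-sided at 5% and there is no true difference. The article gives no correlation between the outcomes, so it is varied. At correlation 0 the rate is 1 − 0.95² = 9.75%; the others come from the bivariate normal distribution.

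| Assumed outcome correlation | At least one false positive |
|---|---|
| 0 | 9.75% |
| 0.5 | 9.1% |
| 0.8 | 7.8% |
| 1 | 5.0% |

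**3. Two outcomes on two contrasts (users versus non-users, and arm versus arm).** The rate depends on how the intervention arm is assembled from its two samples.

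- If equal samples of users and non-users are pooled unweighted, the two contrasts are uncorrelated. At outcome correlation 0 the rate is 1 − 0.95⁴ = 18.5%; at 1 it is 1 − 0.95² = 9.75%.
- If users are weighted to 3% of the arm, the arm mean is almost the non-user mean. The correlation between contrasts is (0.03 − 0.97) / √(2 × 1.9418) = −0.48, where 1.9418 = 0.03² + 0.97² + 1. Two contrasts that share one group have correlation 0.5 in size, so that simulation (2,000,000 runs) is a close stand-in.

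| Assumed outcome correlation | Uncorrelated contrasts | Contrasts sharing a group |
|---|---|---|
| 0 | 18.5% | 17.3% |
| 0.5 | 17.2% | 16.2% |
| 0.8 | 15.1% | 13.9% |
| 1 | 9.75% | 9.1% |

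**4. What 290 per group gives on the arm contrast.** Samples are 290 users, 290 non-users and 290 controls, standard deviation 1, two-sided 5%.

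- Weighted arm: standard error = √(1.9418 / 290) = 0.0818.
  - A 0.3 gain confined to users makes an arm difference of 0.03 × 0.3 = 0.009, or 0.11 standard errors. Power is about 5%.
  - A 0.3 gain across the whole arm is 0.3 / 0.0818 = 3.67 standard errors. Power is about 95–96%.
- Unweighted pooling, 580 against 290: standard error = √(1/580 + 1/290) = 0.0719. A gain confined to users gives 0.15, or 2.09 standard errors, and about 55% power. That half-and-half mixture is not the allocated arm.

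**The case against.** The strongest reply is that this is a condensed journal article. A multiplicity procedure usually sits in the full protocol or the analysis plan, and neither is shown, so its absence here is not a finding. That stands. The point does not depend on it, because the article itself states the lead outcome and the contrast, and states each in conflicting ways. An analysis plan could resolve this only by overriding one of those statements.

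Three stronger readings are tempting, and the text does not support them.

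- *All three pairwise group comparisons on both outcomes are primary, so the error rate is about 21%.* The article never says this. Its named contrast is users versus non-users, and the two groups in the sample-size sentence most naturally refer back to that pair. The three-group work is presented as descriptive and univariate, with caller characteristics, reason for encounter and motives as its examples.
- *Each primary outcome is stated to be tested at 5%.* The Analyses section gives no level. The 5% appears only among the sample-size assumptions, so its use for each test is an inference.
- *A single significant result on safety or satisfaction would drive nationwide implementation.* The Perspectives section ties that decision to the use rate and the assessed relevance of bypassing.

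It is also fair to object that making the arms the deciding contrast is more than a change of wording. Step 4 of the working shows why, and the fix allows for it.

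**Conclusion.** The concern holds as an internal inconsistency. Feeling of safety is the main question in one section and an equal partner of satisfaction in three others. Both outcomes are tied to users versus non-users in two places and to intention-to-treat in a third. The sample size provides for a single two-sided 5% test.

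The inflation depends on assumptions the article does not supply: that each test is run at 5%, that no difference is real, and how far the outcomes correlate. On one contrast the rate is about 8–10% for correlations of 0.8 to 0, and there is no inflation at correlation 1. On both contrasts it is about 14–19%, or about 9–10% at correlation 1. Subgroup analyses would add to this if they too were read as confirmatory. Whether users versus non-users is a sound basis for a causal claim is a separate question.

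**What to change.** Make Primary outcome measures, Study period and power calculations, Response rate and Analyses agree on one lead outcome and one primary contrast.

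1. Test feeling of safety first, at two-sided 5%. Use the general safety item that Table 3 lists for all three groups, not the button-specific item asked only in the intervention arm.
2. Test satisfaction on the same contrast at 5%, only if the first test is significant.
3. Label the other contrast and all subgroup analyses exploratory, reported with confidence intervals.

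**Cost.** Satisfaction cannot be claimed if feeling of safety is not significant. The sequence keeps the full 5% for the first test. Splitting 5% over the two outcomes would instead lower power at 290 per group from 95% to about 91%, or require 336 per group.

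**If the arms are chosen as the primary contrast**, wording alone is not enough. Users and non-users are sampled separately, so they must be weighted back to their shares of the arm. Power must also be restated, because 290 was derived for a 0.3 difference between users and non-users. About 95% remains only if the whole arm gains 0.3, and it falls to about 5% if the gain is confined to the roughly 3% who press the button. If users versus non-users is kept as primary, the 290 stands, and the intention-to-treat analysis is the one to label exploratory.

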## Discussion

A strength of this study is the valid and easy-to-use method of collecting data from triage professionals, i.e. a pop-up questionnaire on their work station [15]. This method lowers the risk of recall bias in the triage professionals because the pop-up questionnaire is completed immediately after the patient contact. Additionally, the large patient flow into the OOH-PC/MH-1813 services in the two regions enables us to include a considerable number of callers in a relatively short time period. Furthermore, the use of an intervention in two organizations with differences in terms of access, triage professional profile and waiting time, and yet similar patient populations, will allow us to explore the use of the intervention in detail. The use of a robust intervention makes it possible to later implement the intervention into other similar OOH-PC settings relatively easily. Also, we have performed a field test of the emergency access button and the questionnaires and have also conducted focus group interviews, which showed that both questionnaires were easy to complete. The obtained information also gave us an idea of the user rate (3%); this is in line with former experiences in the Netherlands, which suggest that overuse is not a serious risk.

However, the fairly low participation rate from both triage professionals and callers constitutes a limitation of this study. We found that 38% of all callers declined to participate and another 10% did not type in their CRN, which is a potential source of selection bias. The level of assessed urgency might be higher among these callers, and they may feel that they are not in a state to participate in surveys. The response rate for the caller questionnaire was approximately 40% in the field test. Even though this is comparable to similar studies [19], this could induce further selection bias. We plan to distribute the caller questionnaire by digital post, which is expected to give a higher response rate. Furthermore, the data collection with use of reminders could introduce recall bias. A reminder will be sent one and two weeks after the contact; the reasons for using the button might be difficult to retrieve at this time point. To reduce this risk, we have predefined categories to help the caller.

### Perspectives

Firstly, this study will provide knowledge on the feasibility and the effects of implementing an option to bypass the telephone waiting line in OOH-PC and the MH-1813. A well-functioning option to bypass the telephone waiting line in case of emergency may improve the access of acute out-of-hours services in Denmark as well as limit non-relevant use of the EMDC-112.

Secondly, even though the percentage of callers who may benefit from bypassing the waiting line is expected to be relatively limited, the total number of contacts to OOH-PC and the MH-1813 is extensive, which means that the absolute number of patients who actually benefit from this simple intervention is likely to be substantial. As the waiting time in the OOH-PC telephone services is a known source of frustration to most people [11], an option to bypass the waiting line for acute matters could potentially provide greater satisfaction and feeling of safety in many people.

Moreover, it will be studied whether callers will manage to use such a bypass option as intended. On the basis of the field study, our estimates suggest that 3% will use the emergency button; this indicates that the option of bypassing the line will not be misused. Together with an assessment of the relevance of the choice of bypassing, this information can be used to decide whether the intervention should be implemented nationwide.

## Abbreviations

CRN: Civil registration number (social security number)
ED: Emergency department
EMDC-112: Emergency medical dispatch center 112 (emergency number for life-threatening injury or illness and request of emergency ambulances)
GP: General practitioner
MH-1813: Medical helpline 1813 (medical call center operated by nurses and doctors with either no medical specialty or other specialty than general practice)
OOH-PC: Out-of-hours primary care.
